Individuals with EDs (mainly investigated for BN) and highly body dissatisfied women show negative cognitive, emotional as well as altered physiological responses during the exposure to their own body [e.g., (26–28)]. For the assessment of stress reactivity, non-invasive measurements are typically used, e.g., heart rate (HR) and heart rate variability [HRV (29)] as sympathetic stress markers. These are affected by emotional stimuli (30) or stress (31). Studies have shown that individuals with AN have a consistently elevated HRV compared to healthy controls, which seems to normalize during recovery (32). Furthermore, salivary alpha amylase (sAA) is a marker of acute stress (33), highly correlates with blood norepinephrine levels (34, 35), and is thereby a further marker of the central sympathetic nervous system [SNS (36, 37)]. Lastly, cortisol, which is a correlate of an activated hypothalamic-pituitary-adrenal (HPA) axis, has been extensively investigated in EDs, showing both altered basal levels and reactivity (38). A study by Monteleone and colleagues (39) showed that individuals with AN exhibit an asymmetry between the HPA axis and the SNS response to a stressor, with the underweight AN group showing a strong cortisol reactivity but an almost completely lacking increase of sAA (comparable to the control groups).

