## Objectives

Due to the high association of BI disturbances and the development and maintenance of EDs, including AN, psychotherapy with patients with AN in any setting should include modules treating body image disturbances explicitly (8). A need for new, emerging treatments with a focus on brain-based interventions as well as mechanism-based approaches, which are specifically addressing psychopathology and BI disturbances, have been proclaimed (43, 44). While there is data available on the efficacy of body exposure interventions for reducing BI disturbances in women with EDs and high body dissatisfaction (20, 25), there is a lack of available data regarding the efficacy of body exposures with children and adolescents. Furthermore, different EDs are frequently mixed up in the literature, making it difficult to investigate specific processes, which might differentiate between body dissatisfied individuals with EDs and body dissatisfied individuals without EDs. Also, underlying psychophysiological and neurobiological processes during body exposure are still poorly understood. Therefore, the aim of this study is to investigate the short-term efficacy of a computer-based body exposure intervention for adolescents with AN. This group is being compared to an AN-TAU group and a body dissatisfied clinical control group.

The primary research question is: Is body dissatisfaction in adolescents with AN reduced after completing a four-session computer based body exposure intervention, compared to TAU?

Secondary research questions include: (1) Body checking and avoidance: Can four sessions of a computer based body exposure intervention reduce body checking and body avoidance behavior, compared to TAU? (2) Viewing patterns / attentional bias (AB): Can the AB in terms of focusing more on negatively rated body parts, measured via eye tracking, be reduced by a four-session computer based intervention in adolescents with AN, compared to TAU? Are there AN-specific AB modifications in comparison to a body dissatisfied control group also obtaining the intervention? (3) Stress reactivity: Do four sessions of body exposure modify stress reactivity in terms of a physiological habituation, measured via salivary cortisol, sAA, HR and HRV? Are there AN-specific effects in physiological habituation in comparison to a body dissatisfied clinical control group?

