Stress levels and stress reactivity are assessed through multiple measures. Firstly, subjective emotion ratings (anxiety, anger, disgust, stress, and sadness) are obtained on a ten-point Likert scale before, during, directly after, and 30 min after each exposure session. Secondly, participants' cardiac activity is monitored during the exposure sessions using a Scosche^®^ Rhythm 24 Heart Rate monitor. Raw data is further processed using Python (https://www.python.org/). RR intervals (RRI) will be detected by a peak-detection algorithm and outliers will be removed using implemented python libraries (e.g., hrv-analysis 1.0.4 package). Instantaneous heart rate (IHR), as a measurement of heart rate variability (HRV), will be derived following IHR$=\frac{60000}{RRI}$, where RRI are measured in milliseconds (61). Changes in HR/IHR and RRI in relation to the number of exposure sessions, i.e., changes over the course of the four exposure sessions, will be analyzed. Thirdly, saliva samples are taken before, during (10 min into the exposure), directly after and 30 min after the body exposure using Salivettes^®^ (Sarstedt, Nümbrecht, Germany). Cortisol, as well as sAA, levels are subsequently analyzed in the laboratory. To do this, saliva samples are stored at −20°C until processing. When processing begins, the samples are thawed and centrifuged at 2,000 × g and 20°C for 10 min. To analyze salivary free cortisol, a commercial chemiluminescence immunoassay (CLIA; IBL Hamburg, Germany) is used, following the manufacturer's instructions. Similarly, to measure sAA, a quantitative enzyme kinetic method is employed, following a standardized protocol.

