#### Body Exposure Sessions

The four computer based body exposure sessions are identical and involve a guided exposure to the previously taken photographs of the participant's own body on the computer screen. Standardized instructions are played to the participants via audio file and reactions and short descriptions of their body parts will be supervised by the study attendant who is present during the sessions. In the beginning and at the end of each session, there is a 30 s period of free viewing time for each the frontal and lateral photograph. During this time, participants are viewing the pictures without any instruction and eye movements are recorded in order to measure AB. The audio file guides participants in viewing their own bodies on the computer screen for an overall duration of about 30 min. The body exposure follows an adapted version of the manualized treatment program by Vocks and Legenbauer (62), in which participants are guided to look at 12 body parts following a fixed sequence. To assess stress reactivity, four saliva samples are taken before, during directly after and 30 min after the end of the body exposure with emotions being rated at the same times. Heart rate variability will be assessed continuously throughout each session via heart rate monitor. The standardized procedure of a body exposure session is shown in Figure 2.

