### Data Analysis

Research questions will be analyzed in repeated measures (rm)-AN(C)OVAs, considering within-subject and between-subject factors and interpreting—depending on the respective hypothesis—main and/or interaction effects. To test intervention effects on body dissatisfaction, body control and body avoidance, as well as AB comparing AN-INT vs. AN-TAU within the RCT, a 2 × 2-rm-AN(C)OVA (between-subject factor = group: AN-INT vs. AN-TAU; within-subject factor = time: pre, post) will be conducted. To assess modifications within and throughout the body exposure sessions regarding AB, emotion ratings, HR, HRV, as well as cortisol and sAA reactivity slope, a 2 × 4-rm-AN(C)OVA (between-subject factor = group: AN-INT vs. CG-INT; within-subject factor = time: 4 exposure sessions) will be conducted. Potential confounders are derived from a theoretical point of view (e.g., age, depression) and will be included as covariates in the statistical analyses (ANCOVAs). Specific test requirements will be tested prior to performing the full analysis. In case of non-adherence to the test requirements (i.e., normal distribution and variance homogeneity), the outcome measures will be logarithmized and additional non-parametric tests will be calculated. Data will be analyzed using IBM SPSS Statistics software. Significance level will be set at *p* =.05 and effect sizes will be interpreted. Effect sizes for AN(C)OVA results were computed as partial η^2^ ($\eta_{\text{p}}^{2}$), with values $\eta_{\text{p}}^{2}$ <0.06 interpreted as small,.06 ≤ $\eta_{\text{p}}^{2}$ <0.14 as medium and $\eta_{\text{p}}^{2}$ ≥ 0.14 as large effects (64). Correction for multiple testing will be applied if necessary.

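### The heart rate variability outcome is defined as instantaneous heart rate (60000/RRI), so under the only definition given it repeats heart rate and cannot answer the HRV part of secondary question 3

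*Protocol article*

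**What the plan says.** The operational definition is in the Parameters section: "Instantaneous heart rate (IHR), as a measurement of heart rate variability (HRV), will be derived following" the expression 60000/RRI, with RRI in milliseconds. The same section then says what will be analysed: "Changes in HR/IHR and RRI in relation to the number of exposure sessions". The one HRV software package mentioned is cited for cleaning: "outliers will be removed using implemented python libraries (e.g., hrv-analysis 1.0.4 package".

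Elsewhere HRV is a measure in its own right:

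- The Introduction names "heart rate (HR) and heart rate variability [HRV (29)] as sympathetic stress markers".
- Secondary question 3 in Objectives asks about physiological habituation "measured via salivary cortisol, sAA, HR and HRV".
- Body Exposure Sessions says: "Heart rate variability will be assessed continuously throughout each session via heart rate monitor".
- Data Analysis puts both into the 2 × 4 repeated-measures AN(C)OVA of AN-INT against CG-INT: "regarding AB, emotion ratings, HR, HRV, as well as cortisol and sAA reactivity slope".

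**The concern.** A variability measure has to describe how much the beat-to-beat interval fluctuates. The formula given converts each interval into a rate. The article therefore attaches the name HRV to heart rate while treating HR and HRV as two outcomes.

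Three things depend on this:

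- Secondary question 3 asks whether HRV changes over the four sessions and whether any change is specific to AN. The Introduction motivates this with reports of altered HRV in AN that normalises in recovery. A heart-rate outcome does not test that.
- The Strengths and Expected Outcomes section says the pilot will help select modifiable stress markers for a larger multi-centre study. HRV could be kept or discarded there without having been measured.
- A report that followed the text would give a heart-rate finding under two names.

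**Working it through.** The article states no figure to reproduce. The check is of the units and of what the quantity responds to.

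**1. Units (no assumptions).** Inputs from Parameters: IHR = 60000/RRI, RRI in ms. There are 60000 ms in a minute and RRI is ms per beat, so (ms/min) ÷ (ms/beat) = beats/min. IHR is the heart rate implied by one interval, and RRI is its reciprocal up to a constant. Neither is a measure of spread.

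**2. Is a variability index named elsewhere?** Reading Introduction, Objectives, Parameters, Body Exposure Sessions, the Figure 2 caption, Data Analysis, and Strengths and Expected Outcomes together, none names RMSSD, SDNN, spectral power or the standard deviation of IHR. The statement of what is analysed writes IHR together with HR, followed by RRI.

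**3. Illustration of size.** Assumptions, none of them in the article: independent normal RR intervals, mean 800 ms, and IHR summarised by its session mean. To second order, mean IHR ≈ (60000/800) × (1 + CV²) = 75 × (1 + CV²), where CV = SD/800.

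| SD of RRI | CV² | 75 × (1 + CV²) | Simulated mean IHR | Simulated RMSSD | Simulated SD of IHR |
|---|---|---|---|---|---|
| 20 ms | 0.000625 | 75.05 | 75.05 | 28.3 ms | 1.88 |
| 80 ms | 0.0100 | 75.75 | 75.75 | 113.5 ms | 7.83 |

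(200,000 intervals per row. A separate run with 2,000,000 intervals gave 75.05 and 75.78.) Variability rises fourfold and RMSSD rises fourfold (113.5/28.3 ≈ 4.0). Mean IHR moves by 0.70 beats/min, and 0.70/75.05 is about 1%.

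**4. Redundancy with HR across participants.** Assumptions: 46 participants (23 + 23, the planned minimum for the two intervention groups), 1800 beats each, participant mean RRI about 850 ms with SD 110 ms, and RRI SD uniform between 15 and 90 ms, drawn independently of the mean. Over 300 runs, session-mean IHR and session HR (60000/mean RRI) correlated 0.9996 on average (minimum 0.9991). Mean IHR correlated on average 0.01 with SDNN. That second value reflects the independence built into the simulation. If rate and variability are related in the trial's participants, IHR would reflect variability mainly through that relation.

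**The case against.** The strongest reply is that an instantaneous series need not be averaged. The article does not say that it will be, and the spread of the IHR series would be a legitimate variability measure: in the table above, the SD of IHR rises from 1.88 to 7.83. On this view the session summary is a detail that a condensed article may leave to a fuller document, and the cited source for the formula cannot be checked here.

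Part of this stands. The session mean is an assumption, so the 75.0 to 75.8 figure illustrates the problem and is not a property of a stated outcome. The rest does not stand. The article did not leave HRV open: it defined it by formula and then grouped IHR with HR for analysis. It describes no dispersion step and cites the HRV package only for removing outliers. A citation cannot change the units of the printed formula, and a different index in a fuller document would still have to be reconciled with this text.

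A reader might infer more than the article supports, in four respects:

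- **That HRV is never analysed.** Data Analysis lists it. What is missing is a valid definition.
- **That one quantity is tested as three outcomes.** The text already writes HR/IHR as one item beside RRI.
- **That agreement between HR and HRV will be presented as converging evidence.** No section says so, and the stated habituation expectation names HR but makes no HRV prediction.
- **That the trial as a whole is compromised.** AN-TAU attends no exposure sessions, so HRV plays no part in the randomised comparison.

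**Conclusion.** The point holds as a wrong definition of one secondary outcome. The article's only definition of HRV is a heart-rate transform, while Objectives and Data Analysis list HRV separately from HR. That conclusion rests on the units alone. Under the definition given, the HRV part of secondary question 3, including the AN-INT against CG-INT comparison, cannot be answered, and the pilot gives no basis for judging HRV as a marker for the next trial.

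The size of the insensitivity, about 1% in mean IHR for a fourfold change in RRI standard deviation, depends on the assumed 800 ms mean, normal intervals and a session-mean summary. The damage is confined to HRV, one of four physiological markers in that question and assessed in a non-randomised comparison. Body dissatisfaction, AN-INT against AN-TAU, and the planned group sizes do not depend on it. It should be corrected before any HRV analysis is run or reported.

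**What to change.** Name one true variability index as the HRV outcome, for example ln RMSSD, computed from the artefact-corrected RR series that the Parameters section already plans to derive. State the fixed windows in which it is computed. These must lie within the recorded period, which the Figure 2 caption gives as AB Assessment 1 to Stress 3. That period opens with free viewing of the participant's own photographs (30 s each for the frontal and lateral view), so the first window is not a resting or pre-exposure baseline and should not be called one. Report IHR and RRI as heart rate only.

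If no index is to be added, remove HRV as a separate outcome from secondary question 3 and from the 2 × 4 analysis, and describe the cardiac outcome as heart rate wherever HRV is now named.

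The first option costs a few lines in the planned Python processing and a corrected sentence in the text. The second costs wording only. Neither changes the recording schedule.

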### Procedure

For each participant, the whole intervention cycle consists of six sessions and will take place over ~2.5 weeks. After a pre-intervention session, the intervention itself comprises of four body exposure sessions (with a duration of ~45 min each), followed by a diagnostic post-intervention session (with a duration of about 10 min). These are described in more detail below. The body exposure intervention is set upon the body exposure module of the manualized body image treatment program by Vocks and Legenbauer (62). This treatment program has been shown to be a successful technique for improving the outcome of ED treatment in adults (63). The procedure has been adapted for the current study in terms of participants being exposed to photographs of the own body via a computer, instead of using a mirror, and the manualized instructions for each exposure session being transformed into an audio file to ensure a standardized procedure. Throughout all body exposure sessions each participant is guided and accompanied by a permanently assigned female attendant of the research team.

#### Pre-intervention Session

The pre-intervention session starts with the completion of the questionnaires, the attractiveness-ratings of the body parts and the attention test. Furthermore, some theoretical background regarding exposure therapy is explained (psychoeducation). Afterward, two photographs of the participant wearing standardized sportswear (black sports bra and tight shorts; one picture each in frontal and lateral view) will be taken. Lastly, the participant receives an introduction to the eye tracking methodology and the saliva collection technique. For the AN-TAU group, an assessment of AB is taken during this session.

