### Design

Within a randomized controlled trial (RCT) female adolescents and young women with AN are either receiving four sessions of a computer based body exposure intervention (AN-INT) or treatment as usual (AN-TAU). Additionally, a highly body dissatisfied group of clinical control participants (CG-INT) are undergoing the intervention to identify AN-specific processes of the intervention. The study design, including study groups, time points and methods of assessment, is shown in Figure 1. The study includes intraindividual (pre- vs. post-intervention; modifications throughout the four exposure sessions) and interindividual (AN-INT vs. AN-TAU; AN-INT vs. CG-INT) research. The TAU group only completes the pre- and post-intervention sessions with assessment of psychopathology and a recording of gaze patterns.

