### Parameters

Psychopathology is assessed through the completion of multiple questionnaires: Eating disorder psychopathology and body dissatisfaction are assessed by administering the Eating Disorder Inventory-2 [EDI-2 (50), German version (51)], body image avoidance behavior via the Body Image Avoidance Questionnaire [BIAQ (52), German version (53)], and body checking behavior by the Body Checking Questionnaire [BCQ (54), German version (55)]. To assess relevant comorbid symptoms, we are also administering the Beck Depression Inventory-Revised [BDI-II (56), German version (57)] to test for depressive symptoms, and the Fear Survey Schedule for Children-Revised [FSSC-R (58), German version (59)] to test for symptoms of anxiety. Additionally, body parts are rated for self-perceived attractiveness on a seven point Likert-type scale (ranging from very negative to very positive) and participants are asked to list their three most disliked body parts. In order to control for a potential attention deficit we also administer an attention test [d2 test (60).

Attentional bias is assessed by recording gaze patterns during body exposure via the Eyegaze Analysis System^TM^ (Interactive Minds, Dresden, Germany), which is an infrared video-based binocular tracking system (17). In particular, the subsequent analysis is focused on assessing the fixation patterns (duration, frequency) on the previously three most negatively rated body parts, which are defined as regions of interest (ROI). A fixation is counted if the participant's gaze is focused on a specific area for 100 ms or more. Total fixation time for each ROI is calculated and corrected for its size relative to the picture size (17).

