**Figure 2 F2:**
[figure not shown]
Standardized procedure of an exposure session with attentional bias (AB) assessments (1,2) for each frontal and lateral view (30 s each), stress measurements (1-4) via emotion ratings and saliva samples, guided body exposure times (1,2), and heart rate sampling (from AB Assessment 1 to Stress 3).

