#### Post-intervention Session

During the post-intervention session, participants are again asked to complete questionnaires, including the EDI-2, the BIAQ, the BCQ, and the attractiveness ratings of the body parts. For the AN-TAU group, AB is assessed again during this session.

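### Attentional bias appears to be recorded on different occasions in the two randomised arms, so the AN-INT vs AN-TAU pre/post contrast mixes intervention effect with measurement occasion, chiefly at post

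*Protocol article*

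**What the plan says.** **AN-TAU.** The Design section states: "The TAU group only completes the pre- and post-intervention sessions with assessment of psychopathology and a recording of gaze patterns". The Procedure repeats this session by session. For the pre-intervention session it says "For the AN-TAU group, an assessment of AB is taken during this session", and for the post-intervention session "For the AN-TAU group, AB is assessed again during this session".

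**AN-INT.** Gaze recording is described within the exposure sessions. Under Body Exposure Sessions: "In the beginning and at the end of each session, there is a 30 s period of free viewing time", for the frontal and the lateral photograph, during which "participants are viewing the pictures without any instruction and eye movements are recorded in order to measure AB". The caption of Figure 2 likewise lists two AB assessments per exposure session. The Parameters section defines the measure in the same terms: "Attentional bias is assessed by recording gaze patterns during body exposure". The accounts of the pre- and post-intervention sessions mention no AB recording for this arm, although the introduction to eye tracking in the pre-intervention session is not restricted to one arm.

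**Analysis.** Data Analysis places AB in the randomised 2 × 2 repeated-measures model ("as well as AB comparing AN-INT vs. AN-TAU within the RCT") with time levels pre and post. This serves secondary question 2, whether four sessions reduce AB compared with TAU.

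**The concern.** In a group × time analysis, randomisation makes the arms comparable at entry. It does not protect against measuring the outcome under systematically different conditions in each arm. If AN-TAU is measured in stand-alone assessment sessions and AN-INT only inside treatment sessions, arm and occasion coincide exactly. No covariate or model term can then separate them.

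At stake is the randomised answer to secondary question 2. A difference in change could reflect a lasting shift in AB, or it could reflect the state in which AN-INT was measured. The article also says the pilot will inform outcome selection and expected effect sizes for a larger multi-centre study, so a distorted AB effect could be carried forward.

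**Working it through.** The plan gives no figure on this point to reproduce. The check sets the stated occasions side by side; a short calculation then shows how sensitive the test is.

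**Step 1: recordings by occasion, as described.**

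| Occasion | AN-INT | AN-TAU |
|---|---|---|
| Pre-intervention session | none described | 1 |
| Exposure sessions 1–4 | start and end of each: 4 × 2 = 8 | not attended |
| Post-intervention session | none described | 1 |

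No row has recordings in both arms. AN-TAU's interval runs from the first to the last of the six sessions in the cycle. AN-INT's longest possible interval runs from the second to the fifth.

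**Step 2: what can serve as pre in AN-INT.** The free viewing at the start of exposure session 1 is uninstructed and comes before any guided exposure. It is in a later session than AN-TAU's baseline, but it is an untreated measurement. This mismatch is minor.

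**Step 3: what can serve as post in AN-INT.**
- *End of session 4.* All four exposures are complete, but the recording directly follows about 30 minutes of guided viewing of twelve body parts in a set order. Immediate carry-over or fatigue may affect gaze. AN-TAU is never measured in that state.
- *Start of session 4.* There is no same-session carry-over, but only three of the four exposures have been received, while the research question concerns four.

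Neither corresponds to AN-TAU's separate post-intervention session.

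**Step 4: sensitivity of the test (assumed inputs).** The documents give 23 in AN-INT, 15 in AN-TAU and alpha 0.05. The occasion shift c (in SD of AB) and the pre/post correlation ρ are not given, so they are assumed over a range. The 2 × 2 interaction test is equivalent to a two-sample t-test on change scores.

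- SD of change = √(2(1 − ρ)): 1.183, 1.000 and 0.775 for ρ = 0.3, 0.5 and 0.7.
- √(1/23 + 1/15) = 0.332; degrees of freedom = 23 + 15 − 2 = 36.
- Noncentrality = c / (SD of change × 0.332). For ρ = 0.5: 0.60, 0.90 and 1.51 at c = 0.2, 0.3 and 0.5.

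Rejection rate of the two-sided 5% test when the intervention has no effect on AB:

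| c | ρ = 0.3 | ρ = 0.5 | ρ = 0.7 |
|---|---|---|---|
| 0 | 5.0% | 5.0% | 5.0% |
| 0.2 | 7.9% | 9.0% | 11.8% |
| 0.3 | 11.5% | 14.2% | 20.6% |
| 0.5 | 23.6% | 31.1% | 47.3% |

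**The case against.** **The premise is inferred.** Nowhere does the article say that AN-INT is not recorded at the pre- and post-intervention sessions, and Figure 1, which is said to show time points and methods by group, is not shown. This stands as a caveat. It does not overturn the reading: singling out AN-TAU in both session descriptions would serve no purpose if both arms were recorded there. The abstract's remark that AB is measured in every session does not help either, because the same sentence covers cortisol and amylase, which are described only for exposure sessions.

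**Choosing among the eight recordings can be left to a fuller document.** That is fair, and not naming them in the article is no finding. But an analysis plan can only select recordings; it cannot create matched ones.

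**The bias need not favour the intervention.** This also stands. Using the start of session 4 would, if benefit builds up over sessions, tend to understate a four-session effect. Carry-over and fatigue concern only the end-of-session recording, which the article does not select.

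**Stronger readings that the document does not support.**
- A reader might infer that AN-TAU's gaze is primed by questionnaires and ratings at both sessions. The order within the post-intervention session is not given, and AN-INT completes the same ratings at its own pre-intervention session.
- A reader might infer that allocation is disclosed early enough to harm the baseline data. The pre-intervention session begins with the questionnaires, the time of randomisation is not given, and no harm can be shown.
- A reader might take the rejection rates above as this trial's error rate. They rest on assumed shifts.

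**Conclusion.** The point holds for AB in the randomised comparison, on the plain reading of the session descriptions. All AB data in that contrast are affected, but unequally: the baseline difference is minor and the post difference is material. The direction and size of the bias cannot be established from the document or estimated from the trial's data. The calculation shows only that, at 23 vs 15, an occasion shift of 0.2 to 0.5 SD would raise a nominal 5% error rate to between about 8% and 47% over correlations of 0.3 to 0.7.

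It would be wrong to read this as a flaw in the trial's main result. Body dissatisfaction, the BIAQ and the BCQ are collected at pre and post without restriction by arm. The AN-INT vs CG-INT 2 × 4 analysis uses the same in-session occasions in both groups. One part of one secondary question in a pilot is affected, and the remedy is cheap enough to be worth making.

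**What to change.** Record the same uninstructed free viewing (30 s frontal, 30 s lateral) at the pre- and post-intervention sessions in AN-INT as in AN-TAU, at the same point in each session. The article does not describe the format of the AN-TAU recording, so state that it is identical. Use only these recordings in the 2 × 2 AB analysis, and keep the in-session recordings for the 2 × 4 analysis. Giving CG-INT the same pre-intervention viewing would keep the 2 × 4 groups alike in prior sight of the photographs.

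The cost is about one minute of viewing plus tracker set-up in each of two sessions already attended. Set-up is not negligible in a post-intervention session of about 10 minutes. There is also one extra brief view of the photographs before session 1. The photographs and the eye-tracking introduction are already part of the pre-intervention session.

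For participants already treated, prespecify the start of session 1 as pre and name the recording used as post. State that the start of session 4 reflects three exposures and that the end of session 4 is open to immediate carry-over. Report the AB contrast for them as exploratory and not occasion-matched. If AN-INT is in fact recorded at both assessment sessions, say so in the Procedure and name those recordings for the 2 × 2 analysis; the point then falls away.
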